### Patient and public involvement

3.13

Patients and public involvement are not planned to involve in this RCT.

## Discussion

4

For CRC patients, the important thing is treating cancer itself, so the importance of optimizing treatment strategies to CRC patients is evident. Quality of life improvement is other object for most CRC patients since it determines the meaning of life of those individuals along with long-term survival benefits.

The results from this RCT will contribute to clinical practice by modified GGQL formula for CRC patients with the type of damp-heat, and guiding future studies on herbal medicine for this subject. Our goal in this study is to accomplish a RCT of high quality that utilizes validated evaluation measures not only for quality of life, effectiveness of treating tumor itself and time of survival in the primary outcomes but also for the tumor microenvironment and immune status of the patients in the secondary outcomes.

### Trial status

4.1

At the time of submission, recruitment will be carried out. Recruitment will start on October 1, 2021 and is expected to be completed on September 30, 2023. It was registered under on September 11, 2021 and is being financed by National traditional Chinese medicine (TCM) clinical research base (Shanxi Province Hospital of Traditional Chinese Medicine) (JDZXLC-02).

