### Trial design

3.1

This multi-centers, randomized controlled clinical trial with parallel groups of 120 CRC patients with the type of damp-heat will be conducted according to the flow diagram and will last for 2 years, scheduled to start in October 2021 (Fig. 1).

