### Procedures (Template)

3.4

CRC patients will be evaluated by an oncologist, and after the initial evaluation, the patient with indication on using modified GGQL formula and fit the eligibility criteria of this RCT will be referred for specific evaluation by an oncologist with at least 3-year experience in the evaluation and prescription of modified GGQL formula. All the included participants would sign terms of free and informed consent.

The participants fitting the criteria of inclusion will be randomized to be divided into two groups: the treatment group (using modified GGQL formula plus basic antitumor therapy) and the control group (basic antitumor therapy).

The first evaluation should occur before treatment and then the participants will accept 12 weeks treatment in the treatment group or the control group. And they will be evaluated each three weeks after interventions.

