### Intervention

3.6

After specific evaluation by an oncologist, the participant will be divided into one of the two groups according to the randomization.

The treatment group: basic anti-tumor therapy combined with modified GGQL formula.

Basic anti-tumor therapies include:

1.mFOLFOX6 (Oxaliplatin 85 mg/m^2^ d1 + Leucovorin 400 mg/m^2^ d1 + Fluorouracil 400 mg/m^2^ d1 + Fluorouracil 2-2.4 g/m^2^ 46 h), the treatment period is 14 days; or2.FOLFIRI (Irinotecan + Leucovorin 400 mg/m^2^ d1 + Fluorouracil 400 mg/m^2^ d1 + Fluorouracil 2–2.4 g/m^2^ 46 h), the treatment period is 14 days; or3.XELOX (Oxaliplatin 85 mg/m^2^ d1 + Capecitabine 850–1000 mg/m^2^ bid d1-14), the treatment period is 21 days.

Modified GGQL formula is mixing and powdering by *Gegen*, *Huangqin*, *Huanglian*, *Muxiang*, *Chunpi*, *Donggua’er*, and *Paojiang*, which offered by Preparation Center of Shanxi Province Hospital of Traditional Chinese Medicine. The patients are planned to be used modified GGQL formula for 12 weeks.

The control group: basic anti-tumor therapy (the same as above).

All patients will be supervised by an experienced oncologist during this study.

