### Primary outcome measures

3.7

1.Quality of life: measured by SF-36 at the baseline, week 6 of treatment, and week 12 of treatment;2.TCM symptom score: measured by the form of TCM symptom at the baseline, week 6 of treatment, and week 12 of treatment;3.Progression-free survival (PFS): measured by follow-ups;4.Overall survival (OS): measured by follow-ups.

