### Secondary outcome measures

3.8

1.Performance status: measured by Karnofsky score at the baseline, week 6 of treatment, and week 12 of treatment;2.Size of tumor: measured at the baseline, week 6 of treatment, and week 12 of treatment;3.Tumor marker in the serum: measured at the baseline, week 6 of treatment, and week 12 of treatment;4.Tumor microenvironment: measured by vascular endothelial growth factor receptor (VEGFR) and Th1/Th2 in the serum at the baseline, week 6 of treatment, and week 12 of treatment;5.Immune status: measured by subset of the class of T-cells in the serum at the baseline, week 6 of treatment, and week 12 of treatment.

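### The stated two-year trial duration equals the recruitment window, leaving no time for the last patients' 12 weeks of treatment or for survival follow-up after the last enrolment

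*Protocol article*

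**What the plan says.** All references are to the protocol article.

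- Trial design (3.1): the trial "will last for 2 years, scheduled to start in October 2021".
- Trial status (4.1): "Recruitment will start on October 1, 2021 and is expected to be completed on September 30, 2023".
- Procedures (3.4): "the participants will accept 12 weeks treatment in the treatment group or the control group". Intervention (3.6) gives the same 12 weeks for the herbal formula.
- Primary outcome measures (3.7): "Quality of life: measured by SF-36 at the baseline, week 6 of treatment, and week 12 of treatment". The TCM symptom score has the same schedule. Of the two survival primaries, the first reads "Progression-free survival (PFS): measured by follow-ups", and OS is described in the same way. The article gives no length of follow-up and no closing date for either.
- Sample size calculation (3.10): the planning figures are a median OS of 25 months (treatment) and 22 months (control), with 1-year survival of 80% and 75%. The total is 120 patients with 20% drop-out.

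**The concern.** A trial period has to contain recruitment, the last patient's treatment and whatever follow-up the endpoints need. Here recruitment uses all of it. This is a conflict between dates the article states, so it is not a detail left to a fuller protocol.

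Two things are at stake if the calendar is followed as written. Late entrants would lack the week-12 value of two primaries (SF-36 and TCM symptom score) because of their entry date alone. OS, a declared primary and the basis of the sample-size paragraph, would be read when most patients are still censored.

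**Working it through.** **1. The calendar.** 1 October 2021 to 30 September 2023 inclusive is 730 days, which reproduces the stated two years. Treatment takes 12 × 7 = 84 days.

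- Last entry date that still reaches week 12 by 30 September 2023: 30 September − 84 days = 8 July 2023.
- Week 12 for a patient entered on the last day: 30 September + 84 days = 23 December 2023.
- Section 3.1 names only the month. If the two years ran as late as 31 October 2023, the last entrant would have 31 days, still short of 84.

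**2. Share unable to reach week 12.** Assuming uniform accrual (the article gives no accrual pattern): 84/730 = 11.5%, and 0.115 × 120 = 13.8, about 14 patients.

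**3. Potential OS follow-up at 30 September 2023.** It ranges from 0 to 24 months, mean 12, and half the patients have at least 12 months. The 25-month median exceeds the maximum. Only patients entered in the first 24 − 22 = 2 months could be observed to 22 months: 2/24 × 60 = 5 controls.

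**4. Expected deaths.** Assume exponential survival, uniform accrual over A = 24 months, and a minimum follow-up of F months after the last entry. With hazard λ,

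P(death) = 1 − [exp(−λF) − exp(−λ(A+F))]/(λA).

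With F = 0:

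| Planning figures used | λ treatment; λ control | P(death) | Deaths among 120 |
|---|---|---|---|
| Medians 25 and 22 months | ln2/25; ln2/22 | 0.270; 0.298 | 60 × 0.568 = 34.1 |
| 1-year survival 80% and 75% | −ln(0.80)/12; −ln(0.75)/12 | 0.193; 0.240 | 60 × 0.433 = 26.0 |

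The two rows differ because exponential medians of 25 and 22 months imply 1-year survival of about 72% and 69%, not 80% and 75%. The range is therefore 26 to 34 deaths (22% to 28%). With 96 patients (120 less 20%) it is about 21 to 27.

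**5. Effect of a later cut-off, N = 120.**

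| F (months) | Deaths, medians | Deaths, 1-year rates | Log-rank power, HR 22/25 = 0.88 |
|---|---|---|---|
| 0 | 34 | 26 | about 6% |
| 12 | 60 | 47 | about 7% |
| 24 | 78 | 63 | about 8% |

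Power uses Schoenfeld's formula, two-sided 0.05, with the deaths from the medians. By the same formula, 80% power at HR 0.88 needs 1,922 deaths. The hazard ratio implied by the 1-year rates, ln(0.80)/ln(0.75) = 0.776, needs 487.

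**The case against.** The strongest reply is that nothing in the article says data collection closes on 30 September 2023. Follow-up may continue past that date, in which case 3.1 is loosely worded. Or 4.1 may give the trial's end as the end of recruitment. The flow diagram that 3.1 relies on is not available here, and the eligibility criteria (3.3.1) require a telephone number and address for follow-up. This stands to the extent that the losses above belong to the literal reading and are not certain. It does not remove the contradiction, because on either alternative one of the two sections has to be corrected.

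A reader might infer four stronger points, which the documents do not support:

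- **Almost no follow-up.** True only of late entrants. The mean is about 12 months.
- **PFS mostly censored, its median not estimable.** The article gives no PFS assumption. With assumed PFS medians of 6 to 12 months (not in the documents), about 79 to 55 of 120 patients would have an event even by 30 September 2023.
- **No scheduled assessment of progression after week 12.** The timetable "2.Size of tumor: measured at the baseline, week 6 of treatment, and week 12 of treatment" belongs to a secondary endpoint. PFS is assigned to follow-ups, and Procedures (3.4) mentions evaluation every three weeks after the interventions. That wording is ambiguous, but it rules out asserting that assessment is absent.
- **Longer follow-up would make the OS comparison conclusive.** It would not: power stays below 10% at HR 0.88 even with 24 further months.

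**Conclusion.** The point holds as a contradiction between stated dates. The two-year trial duration in 3.1 and the two-year recruitment window in 4.1 cannot both stand with 12 weeks of treatment, week-12 primaries and survival follow-up.

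Followed literally, about one patient in nine misses week 12 inside the trial. That rests on uniform accrual, and more patients would be lost if accrual is heavier late in the window. OS would be immature, with roughly 72% to 78% of patients still alive at the close. This figure also rests on exponential survival at the article's own planning figures. The conflict itself needs neither assumption. The conclusion covers the week-12 primaries and OS; no comparable claim is made for PFS.

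**What to change.** - Reconcile 3.1 and 4.1 by stating the end of recruitment and the end of the trial as separate dates, with the trial end at least 12 weeks after the last enrolment.
- Set the OS/PFS data cut-off at a fixed minimum interval after the last randomisation and state the expected number of deaths. Twelve months, for example, gives follow-up of 12 to 36 months and about 60 deaths under the planning medians (about 47 under the 1-year rates). Vital status can be collected through the telephone contact already required at entry.
- If the end date cannot move, close recruitment at least 12 weeks earlier (by about 8 July 2023) and report OS descriptively.

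The cost is date changes in two sections, telephone follow-up of patients already enrolled, and a later final OS report. The gain is that every patient has time to reach week 12 and the OS estimates are more mature. The mismatch between N = 120 and the survival assumptions remains and has to be dealt with separately.
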